### Primary outcome

The primary outcome of the intervention is the change in depressive symptoms rated by the clinical global impression of change (CGI). The CGI is performed by the clinician and includes a 1- to 7-point rating scale of the global improvement due entirely to treatment [34].

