### Outcome measures

All outcomes will be measured by trained and experienced assessors from nursing and medical staff members, blinded to group allocation. With written consent to participate, patients were assigned an identification number (ID). The consent forms are kept in a locked cabinet for 10 years. All other data is stored via the hospital information system.

In cases of accident or injury, concerns of the medical staff members or unwillingness of patients to participate during the interventions, unblinding is permissible. For participants who suffer unexpected harm from trial participation receive medical care. The intervention will be modified immediately in response to harms or worsening patient’s conditions. If no improvement is achieved, the patient will be excluded from the study. Other criteria of discontinuing are, concerns of medical team members or if the patient withdraws his participation in the intervention. Adverse events related to the intervention are documented in detail.

Primary and additional outcome variables are presented in Table 2. The time points for the primary outcome measures are a maximum of 1 week pre- and post-intervention. The adherence to intervention and the documentation of adverse events will be recorded to investigate the feasibility of the exercise intervention. A potential relation of adverse events to the intervention will be evaluated by a senior old age psychiatrist, who is not part of the study team.

**Table 2 Tab2:** Objectives and instrumental set-up of the trial

	Variable	Instrument
**Primary outcome**	Depressive symptoms	CGI – Global improvement scale [34]
**Secondary outcome**	Depressive symptoms	BDI II [35] HAMD [36]
	Physical (in)activity	Body fixed Motion Sensor (McRoberts, The Hague, NL)
	Endurance performance	6-min walk test [37]
	Application of antidepressive medication	Fluoxetin equivalents (FED) [38]

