### Analysis

The trial will be analyzed by using the intention-to-treat principles, in which all patients with baseline data are included in the analysis. Adherence to intervention will be collected descriptive at each training session. The data are stored on the clinic’s own servers, which comply with a heightened security system. Missing data that are not directly related to adherence will be imputed, in order to include all participants. Differences between IG and CG from baseline to post-intervention will be determined by one-way repeated measure ANOVA for parametric and normally distributed data or the Friedman one-way repeated measure analysis of variance for non-parametric or non-normally distributed data. The level of significance is set at alpha ≤ 0.05. All computations will be performed using SPSS software (IBM Corporations, Armonk, NY, USA). No committee for data monitoring and auditing is planned.

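### The primary outcome is a rating of change with no baseline value, yet it is timed, sized and analysed as a pre/post pair, so the stated primary analysis cannot be carried out

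*Protocol article*

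**What the plan says.** **Endpoint.** Under Primary outcome, the protocol article defines the outcome as the "change in depressive symptoms rated by the clinical global impression of change (CGI") and says that the instrument "includes a 1- to 7-point rating scale of the global improvement due entirely to treatment". Table 2 lists it as "CGI – Global improvement scale". The abbreviation list also expands CGI as an impression of change. The text and Table 2 name no CGI severity scale.

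**Timing.** Under Outcome measures: "The time points for the primary outcome measures are a maximum of 1 week pre- and post-intervention".

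**Sample size.** The Sample size calculation section gives 100 patients (50 per arm) for d = 0.5, two-tailed, alpha 0.05 and power 0.95. It lists two measurements and a non-parametric analysis among the inputs.

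**Analysis.** The Analysis section has one sentence on testing, for all outcomes: "Differences between IG and CG from baseline to post-intervention will be determined by one-way repeated measure ANOVA for parametric and normally distributed data". Where those conditions fail, the same sentence substitutes a Friedman test.

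**Context.** Assessors are blinded to allocation (Outcome measures). All participants receive usual care, and the control group also receives a seated exercise session (Control group). The Discussion expects usual care, drug therapy above all, to be effective.

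**The concern.** A severity scale is scored before and after treatment, and the difference is the change. An improvement scale works differently: the clinician compares the patient now with the patient then and records the change directly. Before the intervention there is nothing to rate. The article therefore combines an endpoint with one value per patient and a timing rule, a sample size and a test that each need two.

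This matters because it is the primary endpoint and the article states no other test for it. Whoever runs the analysis must either improvise a method after the data are in or invent a baseline. An invented baseline is the worse choice, because a test over time would then credit exercise with improvement that both arms share.

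**Working it through.** **1. What each part of the plan needs**

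| Section | Content | CGI values per patient |
|---|---|---|
| Primary outcome; Table 2 | 7-point improvement rating | 1 (post) |
| Outcome measures | pre and post time points | 2 |
| Sample size calculation | two measurements | 2 |
| Analysis | one-way repeated-measures ANOVA or Friedman, baseline to post | 2 |

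The first row cannot be reconciled with the other three. With one value per patient, a repeated-measures ANOVA or Friedman test has no second occasion to compare.

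**2. If a constant baseline were filled in**

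This step is hypothetical; the article does not propose it. Put every baseline at 4 (no change). Assume that both arms share the same distribution of post scores: 0.08, 0.27, 0.35, 0.20, 0.06, 0.03 and 0.01 for scores 1 to 7. These probabilities are an assumption. They imply 70% improved, 20% unchanged and 10% worse, with no arm effect at all.

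With two occasions, the tie-corrected Friedman statistic is (improved − worse)² / (improved + worse). At the expected counts in 100 patients it is (70 − 10)² / (70 + 10) = 3600 / 80 = 45, against a critical value of 3.84.

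In 2,000 simulated trials under this assumption:
- the Friedman test over time rejected in 100% of runs, and so did the repeated-measures test of time;
- a Mann-Whitney comparison of post scores between arms rejected in 4.95%, close to the nominal 5%.

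**3. The stated sample size**

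Stated: 100 in total, power 0.95. The stated inputs do not reproduce it as a two-group comparison.

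- Normal approximation: n per arm = 2 × [(1.960 + 1.645) / 0.5]² = 103.96, so 104 (208 in total).
- Exact t-test: 105 per arm (210 in total).
- Mann-Whitney, taking its efficiency relative to the t-test as 0.955: 104.93 / 0.955 = 109.9, so 110 per arm (220 in total).

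The versions that come close use a real second measurement. A group-by-time interaction with f = 0.25 (half of d = 0.5) and zero correlation between the two measurements needs 106 in total and has power 0.938 at 100. At correlations of 0.3, 0.5 and 0.7 it needs 76, 54 and 34. A paired t-test at d = 0.5 needs 54 patients. The article states no correlation, and an improvement rating has no first measurement to correlate with.

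**4. Power of a single post rating with 50 per arm**

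- Normal approximation: 0.5 × √(50/2) = 2.50; 2.50 − 1.96 = 0.54; Φ(0.54) = 0.705.
- Exact t-test: 0.697.
- Mann-Whitney, efficiency 0.955: 0.677.

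**The case against.** **The schedule figure is not visible.** Fig. 2 may show how the CGI is scheduled, and its legend calls it only a clinical global impression scale. The text also says that the CGI includes the 7-point rating, which leaves room for other components. This lowers certainty about what is recorded at baseline. It does not remove the conflict, because Table 2 fixes the improvement scale as the primary instrument and no schedule can give that scale a baseline value.

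**A pre-assessment visit is legitimate.** A change rating needs a documented starting state. This stands. The visit is not the error; the error is treating the CGI score as measured there.

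**The analysis sentence is generic.** Its pre/post structure fits the HAMD, BDI-II, walk test and sensor data. This stands too: the defect is that the CGI is not separated out. That a one-way test over time has no group term would be a problem on any scale, and is a distinct weakness that this endpoint makes worse.

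**A stronger reading about blinding.** A reader might infer from the phrase about improvement caused by treatment that the outcome cannot be rated blind, or that raters are pushed to guess the arm in every rating. The documents do not support this. The phrase is a one-line, referenced description of the instrument, and the rater instructions are not shown. Every patient is under treatment (usual care plus exercise or a control session), so a blinded rater can score improvement under overall care. What remains is an ambiguity: treatment is undefined, and a blinded rater cannot separate exercise from usual care.

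**Conclusion.** The point holds and must be fixed. As written, the primary analysis is undefined for the primary endpoint in all 100 patients, since none can have a meaningful pre-intervention improvement score. The contradiction lies within the text itself, between the named instrument on one side and the timing, sample size and test on the other. It is not a detail left to another document.

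Analysed properly as one rating per patient, the planned 100 patients give about 0.68 to 0.70 power at d = 0.5, not 0.95. This assumes two-sided alpha 0.05, no dropout, and that the standardised difference of 0.5 carries over to the CGI score. The Mann-Whitney figure also rests on the efficiency of 0.955. The simulation illustrates what an invented baseline would do under an assumed score distribution; it does not predict this trial's data.

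The wording on attribution to treatment is a minor clarification and carries no share of this conclusion.

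**What to change.** 1. **Primary outcome:** state that CGI improvement is rated once, at post-assessment, against the documented pre-assessment state. Replace the attribution wording with total improvement whatever its cause.
2. **Outcome measures:** remove the pre time point for the CGI score. Keep the pre-assessment visit, which documents the starting state and supplies baseline HAMD and BDI-II.
3. **Analysis:** give the CGI its own sentence, naming a between-arm comparison of the 7-point score as an ordinal outcome: either Mann-Whitney, or proportional odds with baseline HAMD or BDI-II as covariate. Choose one in advance.
4. **Sample size calculation:** remove the two measurements and restate the power for 50 per arm at d = 0.5 as about 0.68 to 0.70. If 95% power is to be kept, about 105 to 110 per arm are needed.

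Items 1 to 3 cost protocol wording and a one-line rater instruction, with no extra assessment. Item 4 costs either an openly lower power or roughly twice the recruitment. The article reports 15 patients recruited by 23 February 2022 but does not say how many already had a post rating. Any such ratings can be kept, with a record of which instruction applied.

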### Secondary outcomes

As a secondary outcome, the symptom domains and the severity of depressive symptoms will be measured by self- and peer-rated assessments. The Beck Depression Inventory (BDI II) [35] is a self-rated scale which is conducted with the patient in interview form. The Hamilton Rating Scale for Depression (HAMD) [36] is performed by the nursing staff members. Mobility-related measurements, such as physical in(activity), will be performed with the Dynaport Move Monitor + (MM+; McRoberts, The Hague, NL). The MM+ consists of an accelerometer, a gyroscope, a magnetometer, a barometer and a temperature sensor. The raw data will be processed using the manufacturer’s own algorithms. The corresponding output includes the type of activity and body positions (walking, stair walking, cycling, shuffling, standing, sitting, and lying) and an additional category not-worn, corresponding MET-values, activity duration, and number of steps per 60-s epoch. Data will be collected for a 48-h period, starting and ending at 12 am on days one and three. The sensor is attached to the lower back approximately 3 cm to the right of the fifth vertebra of the lumbar spine (L5) with a waterproof self-adhesive foil (Opsite Flexifix, Smith and Nephew, London, UK) [39]. The participants will be asked not to remove the sensor during the measurement period.

To assess the endurance performance, the 6-min walk test [37] will be performed at pre- and post-assessment. The patients will be asked to walk a maximum distance in 6 min. The walking speed can be determined by the patient himself and changes and breaks will be allowed.

The applied total dose of antidepressant medication will be assessed by converting the fluoxetin equivalent doses (FED) and the medication on demand in mg/day according to the dose equivalents calculation of Hayasaka et al. [38].

The phases of the trial and the data collection at each timepoints are presented in Fig. 2.

**Fig. 2 Fig2:**
[figure not shown]
SPIRIT figure. TAU, treatment as usual; ICD-10, International Statistical Classification of Diseases and Related Health Problems; MMSE, Mini-Mental Status Examination; CGI, clinical global impression scale; BDI II, Beck Depression Inventory; HAMD, Hamilton Rating Scale for Depression; MM+, Dynaport Move Monitor +

### Intervention

#### Intervention group

Participants allocated to the IG will receive a 2-week ergometer-based aerobic exercise three times per week on non-consecutive days and a duration of 20 min, twice per day. The training can be completed using four different modalities, seated-ergometer bicycles for the upper or lower limb (Emotion Fitness, Inc., USA), rowing ergometer (Concept 2, Inc., USA), or ski ergometer (Perform Better Inc., USA) placed on the hospital wards. This approach is planned to provide low-threshold access and variety in exercise selection, allowing participants to choose a preferred style of moving at each session to complete the weekly requirements. If the patient refuses or is hindered for any reason, the patient is asked to participate once again on the same day. The adherence to the intervention will be recorded by study reports and the training intensity will be monitored by the heart frequency (Polar A300, Polar Electro Oy, Finland).

The training will be performed individually and under constant supervision by research staff. Patients will be instructed on the adequate use of exercise machines before and during each training session. The participant will receive a fitness and activity tracker with a heart rate (HR) monitor (Polar UNITE, Polar Electro Oy, Finland) and be asked to rate the perceived exertion (RPE) with the 6-20 Borg Scale [40] after 10 min (half time of intervention) and after 20 min (end of intervention). The respective training HR will be determined using the formula 220 minus the patient’s age [41]. Each session will begin with a 2 min warm-up of ergometer use with a HR under 50% of the estimated peak heart rate. After 3 min, the participant will be asked to increase the intensity up to 55% of the estimated peak heart rate. After 18 min, the participants will be instructed to decrease the intensity to their own wish to initiate the cool-down. The research staff will collect the exercise data from each session, including the total time of training, average HR and Borg Scores.

#### Control group

Patients allocated to the CG receive a seated relaxation and flexibility exercise with the same level of social interaction as compared to the IG in addition to TAU, which is not expected to show changes [42]. This control intervention is assumed to be an appropriate exercise placebo intervention with very low-intensity exercise, requiring only minimal muscular strength and aerobic capacity. Throughout the study, all participants will receive TAU, such as antidepressants or physiotherapy. It will also include exercise therapy for 45 min twice a week as part of the routine care.

### Analysis

The trial will be analyzed by using the intention-to-treat principles, in which all patients with baseline data are included in the analysis. Adherence to intervention will be collected descriptive at each training session. The data are stored on the clinic’s own servers, which comply with a heightened security system. Missing data that are not directly related to adherence will be imputed, in order to include all participants. Differences between IG and CG from baseline to post-intervention will be determined by one-way repeated measure ANOVA for parametric and normally distributed data or the Friedman one-way repeated measure analysis of variance for non-parametric or non-normally distributed data. The level of significance is set at alpha ≤ 0.05. All computations will be performed using SPSS software (IBM Corporations, Armonk, NY, USA). No committee for data monitoring and auditing is planned.

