**Discussion:**

This short-term aerobic exercise program is expected to decrease depressive symptoms in acute exacerbated periods in older adults. The results may increase the evidence for implementing physical activity interventions in acute hospital settings. The disease-related motivation for exercise in acute exacerbated depressive periods will be the most challenging aspect. The treatment of depression requires new cost-effective approaches, especially in acute geriatric psychiatry with potential benefits for patients, family members, and clinicians.

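### The imputation rule leaves out adherence-related missing data, which on its plain reading conflicts with the intention-to-treat statement beside it; the sentence needs rewriting

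*Protocol article*

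**What the plan says.** Three statements in the Analysis section of the protocol article bear on this.

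- Population: "The trial will be analyzed by using the intention-to-treat principles, in which all patients with baseline data are included in the analysis".
- Missing data: "Missing data that are not directly related to adherence will be imputed, in order to include all participants".
- Method: "one-way repeated measure ANOVA for parametric and normally distributed data or the Friedman one-way repeated measure analysis of variance", the latter for non-parametric or non-normal data.

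Between the first two, the section also says: "Adherence to intervention will be collected descriptive at each training session".

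The Outcome measures section describes how patients leave. On stopping it says: "Other criteria of discontinuing are, concerns of medical team members or if the patient withdraws his participation in the intervention". On patients who are harmed or worsen, and for whom the intervention has been modified, it says: "If no improvement is achieved, the patient will be excluded from the study". It does not say whether the post-intervention assessment is still made for either group.

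The Discussion paragraph of the Abstract says what the investigators expect: "The disease-related motivation for exercise in acute exacerbated depressive periods will be the most challenging aspect".

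**The concern.** The imputation sentence has a stated purpose, to keep everyone in, and a restriction that works against it. If missingness caused by non-adherence is exempt from imputation, those patients have no outcome value and cannot contribute to the comparison. The analysis would then cover fewer patients than the intention-to-treat statement promises.

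The restriction also falls in an awkward place. The protocol links unwillingness to exercise with the illness that the primary outcome measures, so outcomes missing for this reason are less likely to be missing at random than, say, a rating missed for administrative reasons. The arms also differ in what they ask of patients: supervised ergometer training in one, very low-intensity seated exercise in the other. If losses tied to prognosis differ between arms, leaving them out can bias the estimated effect and move the type I error away from 5%.

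**Working it through.** **Step 1: the text.** No figure in the protocol decides this point, so the first check is logical.

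1. The analysis population is everyone with baseline data. Under Allocation, randomisation follows consent and pre-assessment, so this should be close to everyone randomised.
2. Imputation covers missing data unless they are directly related to adherence. Nothing is said about the remainder.
3. Repeated-measures ANOVA and the Friedman test both need each patient's pre and post values. A patient without a post value is not analysed.
4. From 2 and 3, a patient whose post value is missing for an adherence reason drops out. That contradicts 1 and the purpose stated in the imputation sentence itself.
5. The protocol provides a route to such missing values: withdrawing from the intervention is a criterion for discontinuing, and continued assessment is not mentioned.

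Step 4 is an inference from the rule plus the named tests. The protocol nowhere says in words that these patients are dropped.

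**Step 2: possible size.** The protocol gives no dropout rate by arm and no information on how lost patients fare. All inputs here are assumptions except 50 per arm and d = 0.5, which come from the Sample size calculation section.

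Let q be the share of an arm left out and g the amount, in SD, by which those patients do worse than the ones retained. The mean among the retained exceeds the mean of the whole arm by q × g. With the same g in both arms:

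bias = (q_IG − q_CG) × g

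For a 10-point difference in loss:

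- g = 0.25: 0.10 × 0.25 = 0.025 SD, which is 0.025 / 0.5 = 5% of the planned effect.
- g = 0.8: 0.10 × 0.8 = 0.08 SD, which is 0.08 / 0.5 = 16% of the planned effect.

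**Step 3: effect on type I error.** Take a true effect of zero, loss in the intervention arm only, and a two-sample normal approximation with SE = √(1/[50(1 − q)] + 1/50). The rejection probability is Φ(bias/SE − 1.96) + Φ(−bias/SE − 1.96). For q = 10%, SE = √(1/45 + 1/50) = 0.205.

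| Loss in intervention arm (assumed) | Bias for g = 0.25 to 0.8 | Share of d = 0.5 | Type I error |
|---|---|---|---|
| 10% | 0.025 to 0.08 SD | 5% to 16% | 5.2% to 6.8% |
| 20% | 0.05 to 0.16 SD | 10% to 32% | 5.6% to 11.7% |
| 30% | 0.075 to 0.24 SD | 15% to 48% | 6.3% to 19.3% |

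The lower rows need a fifth or more of one arm lost and none of the other. The table treats the outcome as continuous, whereas the CGI is a 7-point rating, so it shows order of magnitude only. If more control patients were lost, the bias would have the opposite sign.

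**The case against.** **The sentence may mean something else.** It comes just after the remark on collecting adherence at each session. It could mean that session attendance, heart rate and Borg scores are reported as observed while all other missing data, outcomes included, are imputed. Nothing in the section would then conflict. This reading is possible but strained: leaving session records unimputed has little to do with keeping every participant in the analysis. The wording does not settle it, so two analysts could follow it and analyse different sets of patients.

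**Non-adherence is not the same as a missing outcome.** This stands. Participants are inpatients with a median stay of 32 days against a 2-week programme, the CGI is rated by a clinician, and the assessment window runs to a week after the intervention. A patient who refuses sessions but stays on the ward can still be rated and analysed. A reader might infer that the primary analysis becomes a per-protocol comparison. The protocol does not support that, because only patients with no post-assessment are affected.

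**Direction of bias.** A reader might infer that loss will be heavier in the ergometer arm and so favour it. The difference in demands makes this plausible, but control patients also attend sessions, and the main Discussion expects good adherence because training takes place on the ward with several sessions in a day. The direction is undocumented.

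**Knowledge of the arm.** A reader might infer that missing values would be classified by someone who knows the allocation. The protocol does not say who classifies them, when, or whether blinded.

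**Power.** Losing 10% of both arms lowers power at d = 0.5 (two-sided 0.05, normal approximation) from 0.705 with 50 per arm to 0.660 with 45. That loss comes mainly from the missing outcomes, not from the rule, and imputation recovers little unless the auxiliary variables predict well. That 0.705 differs from the stated 0.95 is a separate sample-size matter.

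**Level of detail.** An article may leave the imputation model to a fuller plan, and its absence is not the complaint. The complaint is about a rule that the article does state.

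**Conclusion.** The point holds in a limited form. On its plain reading, the imputation rule removes patients whose post-assessment is missing for adherence reasons, and this contradicts both the intention-to-treat statement and the rule's own purpose. On the alternative reading there is no contradiction, but the sentence does not say so. Because it decides who enters the primary comparison, it should be rewritten whichever meaning was intended.

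The protocol gives grounds to think such losses may be informative and may differ by arm, but no figures. With a 10-point difference in loss and a gap of 0.25 to 0.8 SD, both assumed, the bias is 0.025 to 0.08 SD, or 5% to 16% of the planned effect. It grows in proportion to either input. A gap of 2 SD would give 0.10 × 2 = 0.20 SD, or 40% of the planned effect, but nothing in the protocol supports a gap that wide, so it should not be taken as the expected size.

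**What to change.** Replace the imputation sentence with wording to this effect:

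- All randomised patients are in the primary analysis, in the arm to which they were allocated.
- Post-intervention assessment is sought for every patient, regardless of adherence or discontinuation of the intervention, unless consent to assessment is withdrawn.
- Missing outcomes are imputed whatever the reason, using arm, baseline scores and recorded session attendance.
- One sensitivity analysis assigns less favourable outcome values to patients whose outcome is missing for adherence reasons.

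If only session records were meant to stay unimputed, say so in a separate sentence. In Outcome measures, distinguish stopping the intervention from leaving the study, so that it is clear who is still assessed. This concerns data collection only and takes no position on when the intervention should be stopped. The detailed imputation model can sit in the analysis plan.

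The cost is a few sentences and a little programming. Session attendance is already recorded. The only added fieldwork is the post-assessment of patients who stopped the intervention but can still be reached.

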### Sample size calculation

The required calculation of the sample size is performed by using G*Power 3.1 [31]. Based on the results of the current state of studies [24] a moderate effect size is assumed for the change in depressive symptoms. The effects of Bridle’s pooled analysis show an effect size of -0.44 SMD for studies with an active control group. This corresponds most closely to the present methodology with an active control group. The sample required to detect statistically significant differences in the depressive symptoms for a two-tailed test of the proportions with an effect size of d=0.5 was calculated for the primary objective. Based on this calculation, we will include 100 patients in the trial, with 50 allocated to each study group. The allocation rate is 1:1, two measurements, non-parametric analysis due to ordinal characteristics of the instruments and a-error of 0.05 and a power of 0.95 (1-ß-error) according to Cohen [32].

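### The ANOVA-or-Friedman rule assigns no outcome to a branch, so for walk distance, sensor activity and fluoxetine equivalents the test and the estimand depend on the observed distribution

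*Protocol article*

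**What the plan says.** The Analysis section opens its rule with "Differences between IG and CG from baseline to post-intervention will be determined by" and then offers two routes: a one-way repeated-measures ANOVA "for parametric and normally distributed data or the Friedman one-way repeated measure analysis of variance for non-parametric or non-normally distributed data". It names no outcome, gives no criterion for normality, and sets alpha at 0.05.

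The Sample size calculation section rests on a "non-parametric analysis due to ordinal characteristics of the instruments". The same paragraph describes the calculation as being "for a two-tailed test of the proportions with an effect size of d=0.5".

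The Primary outcome section says that the CGI "includes a 1- to 7-point rating scale of the global improvement due entirely to treatment". Table 2 lists the secondary outcomes: BDI-II, HAMD, sensor-measured physical (in)activity, the 6-min walk test and fluoxetine equivalents of antidepressant medication.

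**The concern.** Whether data are normally distributed can be judged only once they have been collected. A rule that turns on this settles the test late. Here the two branches also answer different questions: ANOVA concerns means, and a rank method concerns ordering. The sample size section had already settled the measurement level of the rating scales without data, so the Analysis section could have named the method outright.

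At stake is what each result will mean. Two outcomes of the same kind could be reported on different effect measures because one sample happened to fail a normality check. An analyst who has seen both p-values would also have room to argue for either branch, since no criterion is written down.

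**Working it through.** **1. Which outcome goes where, on the text alone.** ANOVA requires data that are both parametric and normal. The Friedman test takes data that are either non-parametric or non-normal.

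| Outcome | Settled by measurement level? | Settled by the observed distribution? |
|---|---|---|
| CGI, 7 categories | Yes, if the sample size section is read into the rule | Also yes in practice (step 2) |
| HAMD, BDI-II | Arguably, since that section says instruments in the plural | Otherwise yes |
| 6-min walk, sensor activity, fluoxetine equivalents | No, these are not ordinal ratings | Yes |

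**2. A normality check on a 7-point rating.** The documents give no CGI distribution, so one was assumed, with category probabilities 0.05, 0.20, 0.35, 0.30, 0.06, 0.03 and 0.01. All 3,000 samples of 100 failed Shapiro-Wilk at 0.05. A separate simulation (latent normal cut at six assumed thresholds, n = 50) also failed in 100% of samples. The CGI therefore reaches the rank branch on either route.

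**3. A continuous score with moderate skewness.** Assumed: gamma data with shape k (skewness 2/√k), 50 per arm, rank branch taken if either arm fails Shapiro-Wilk at 0.05, 4,000 trials per scenario.

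| k | Skewness 2/√k | Trials taking the rank branch |
|---|---|---|
| 20 | 0.45 | 33% |
| 10 | 0.63 | 56% |
| 5 | 0.89 | 82% |

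At the extremes the branch is nearly determined. Normal data passed a check on pooled residuals in about 95% of trials, and gamma data with k = 2 (skewness 2/√2 = 1.41) passed in 0.03%. In between, the same true distribution can yield either analysis.

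**4. What the switch does to error and conclusions.** Neither named test compares arms (step 5), so a t-test and a Mann-Whitney test stand in as a between-arm version of the rule. There were 50 per arm and 3,000 runs, and the test was chosen by Shapiro-Wilk on pooled residuals.

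| Quantity | Normal data | Gamma, k = 2 |
|---|---|---|
| No arm difference: t-test rejects | 4.2% | 4.9% |
| No arm difference: Mann-Whitney rejects | 4.5% | 4.5% |
| No arm difference: rule applied mechanically | 4.3% | 4.5% |
| No arm difference: more favourable test reported | 5.3% | 6.4% |
| d = 0.5: t-test power | 70% | 70% |
| d = 0.5: Mann-Whitney power | 68% | 84% |
| d = 0.5: tests disagree on significance | 6% | 16% |

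The Monte Carlo standard error at 5% is √(0.05 × 0.95 / 3,000) = 0.4 percentage points, so 4.3% and 4.5% are compatible with 5%. In the moderate-skewness scenarios of step 3, the tests disagreed in 7-9% of trials at d = 0.5, and reporting the more favourable one gave 5.7-5.9%.

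**5. Do the named tests compare the arms?** A one-way repeated-measures ANOVA and a Friedman test on two time points both test change over time. With both arms improving by the same assumed 0.8 SD, so with no arm difference, both rejected in all 3,000 runs.

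**6. Does fixing a rank test cost power?** With n = 50 per arm, d = 0.5 and two-sided 0.05, power is Φ(d√(n/2) − 1.96).
- Mean-based: Φ(0.5 × 5 − 1.96) = Φ(0.54) = 0.705.
- Rank-based, with efficiency 3/π under normality: the effective n is 50 × 3/π = 47.7, giving Φ(0.5 × √23.87 − 1.96) = Φ(0.48) = 0.685.

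The price is about 2 percentage points. Both values lie below the planned power of 0.95. For that power the same inputs need 2 × ((1.960 + 1.645)/0.5)² = 103.96, so 104 per arm or 208 in total by the mean-based formula. The stated total of 100 is not reproduced. That is a separate matter and does not bear on the switch.

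**The case against.** A reader might infer that the primary test itself is open until the data are seen. The documents do not support that. ANOVA requires data to be parametric as well as normal, the sample size section classes the instruments as ordinal, and the CGI is a 7-point rating. On the ordinary reading it goes to the rank branch by measurement level. If it were left to a normality check, it would end there anyway (step 2). What stands against the plan is narrower: the Analysis section never says so for the primary outcome.

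A reader might also infer a materially inflated error rate. The rule assigns one test per type of data and does not offer two p-values. Followed mechanically, it keeps alpha near 5%. The figures above 5% arise only if someone departs from the rule, and they are small.

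Two further objections have weight. The simulation replaces the named tests with between-arm tests and assumes the distributions, so its rates illustrate the mechanism and do not predict this trial. And requiring means for HAMD and BDI-II would be a preference that conflicts with the sample size section, so it is not part of this point.

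It can also be said that the test per outcome is detail for an analysis plan that is not shown. That would answer a complaint about silence. Here the protocol states a rule, and for three secondary outcomes the rule depends on the data.

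**Conclusion.** The point holds as a defect in a stated rule, of moderate importance. For 6-min walk distance, sensor activity and fluoxetine equivalents, the test and the quantity estimated depend on the observed distribution. For the CGI, and arguably HAMD and BDI-II, the rank branch can be inferred but is not written down.

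The harm is an estimand not fixed in advance, together with some room for choice. It is not a meaningful loss of type I error control. The text argument needs no assumptions. The rates rest on assumed distributions, on Shapiro-Wilk at 0.05 as the unstated criterion, and on between-arm substitutes for the named tests.

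**What to change.** Delete the normality switch from the Analysis section and, before unblinding, name one between-arm analysis and one effect measure for each outcome.

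- **CGI:** a Mann-Whitney or proportional-odds comparison of IG with CG, consistent with the non-parametric premise of the sample size section.
- **HAMD and BDI-II:** ranks or means, at the sponsor's choice, but fixed now. If means are chosen, the sample size section's description of the instruments must be reconciled with that.
- **6-min walk, the chosen activity variable and fluoxetine equivalents:** one between-arm method each, set by the measurement scale and kept whatever a normality check shows.

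Each named method must contain the IG-versus-CG contrast. Keeping only the ANOVA or only the Friedman test as written would remove the switch and still leave no comparison of the arms.

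The cost is a few sentences, with no change to data collection or patients. The Trial status section reports 15 participants recruited by the version date, against a target of 100, so at that date the change could still be made early in the trial.
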